#### Tertiary outcomes

We will use the following statistical procedures to evaluate the study tertiary outcomes:*Need for antipsychotic agents*: The differences in the cumulative incidence of need for antipsychotic agents during ICU stay between the FFVM and RFVM groups will be compared using generalized estimating equations with adjustment for the cluster effect, period effect, and interaction between intervention and period. This outcome will be presented as RR and 95% CI.*Need for mechanical restraints*: The differences in the cumulative incidence of need for mechanical restraints during ICU stay between the FFVM and RFVM groups will be compared using generalized estimating equations with adjustment for the cluster effect, period effect, and interaction between intervention and period. This outcome will be presented as RR and 95% CI.*Unplanned loss of invasive devices*: The differences in the cumulative incidence of any unplanned loss of invasive devices (venous catheter, enteral tube, or urinary catheter) during the ICU stay between the FFVM and RFVM groups will be compared using generalized estimating equations with adjustment for the cluster effect, period effect, and interaction between intervention and period. This outcome will be presented as RR and 95% CI.*Coma-free days at day 7*: The number of coma-free days will be evaluated using the 7-day time horizon. Coma-free days will be set to 0 for patients who have died. The differences in the mean proportion of days free of coma (RASS [23] – 4 or − 5) between the FFVM and RFVM groups will be compared using generalized estimating equations with adjustment for the cluster effect, period effect, and interaction between intervention and period. This outcome will be presented as MD and 95% CI.*ICU-acquired pneumonia*: The differences in the cumulative incidence of ICU-acquired pneumonia between the FFVM and RFVM groups will be compared using generalized estimating equations with adjustment for the cluster effect, period effect, and interaction between intervention and period. This outcome will be presented as RR and 95% CI.*ICU-acquired urinary tract infection*: The differences in the cumulative incidence of urinary tract infection between the FFVM and RFVM groups will be compared using generalized estimating equations with adjustment for the cluster effect, period effect, and interaction between intervention and period. This outcome will be presented as RR and 95% CI.*ICU-acquired bloodstream infection*: The differences in the cumulative incidence of bloodstream infection between the FFVM and RFVM groups will be compared using generalized estimating equations with adjustment for the cluster effect, period effect, and interaction between intervention and period. This outcome will be presented as RR and 95% CI.*Self-perception of involvement in patient care among the family members*: The self-perception of involvement in patient care will be evaluated using a score developed for the present study, which is composed of 9 questions related to the self-perception of involvement of the family member in the care of the patient in the following domains: (1) re-orientation activities, (2) pain control, (3) mobilization, (4) feeding, (5) hygiene, (6) emotional support, (7) helping patients to interpret ICU staff orientations, (8) helping the ICU professionals to understand patient needs, and (9) helping to create a patient-friendly environment in the patient room. The score of each question ranges from 0 (never involved in the activity) to 3 (very frequently involved in the activity). The total score, which varies from 0 (no involvement) to 27 (maximum degree of involvement), will be obtained by the sum of the scores of each question. The differences in the mean total scores of self-perception of involvement in patient care between the FFVM and RFVM groups will be compared using generalized estimating equations with adjustment for the cluster effect, period effect, and interaction between intervention and period. This outcome will be presented as MD and 95% CI.*Satisfaction among ICU professionals*: The satisfaction of ICU professionals will be evaluated through the score of the following question: Are you satisfied with the current visiting policy of your ICU? The responses to this 5-option Likert scale question may be one of the following: 0 - unsatisfied, 1- somewhat dissatisfied, 2 - indifferent, 3 - somewhat satisfied, 4 - very satisfied. The differences in the mean score values between the FFVM and RFVM groups will be compared using generalized estimating equations with adjustment for the cluster effect. This outcome will be presented as MD and 95% CI.

No adjustment for multiple comparisons will be made for tertiary outcomes. Therefore, the results of tertiary outcomes should be considered exploratory.

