## Statistical analysis plan

### Overall principles

The main analysis for each outcome will be performed at the subject level using the intention-to-treat (ITT) principle, meaning that all participants with a recorded outcome will be included in the analysis and will be analyzed according to the treatment group to which they were randomized (FFVM or RFVM), independent of actual visiting hours. Moreover, all analyses will account for the cluster-randomized crossover design to ensure correct type I error rates and confidence intervals (CIs). A significance level of 0.05, adjusted for multiple comparisons when appropriate, will be used for all statistical comparisons. Analysis will start once all data to discharge for the last included patient have been obtained, the database has been cleaned and locked, and the SAP has been submitted for publication. The R Development Core Team software will be used for analysis [18].

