### Definition of analysis sets

At the cluster level, the ITT population includes all randomized ICUs that recruited subjects, regardless of the degree of adherence to the study interventions or achievement of the patient recruitment goal (50 patients per ICU). At the subject level, the ITT population includes all participants, regardless of protocol deviations. This includes patients who did not receive any ICU visits and family members who did not visit patients during the ICU stay, as well as patients who received visits longer than the maximum limit of visiting hours in both study periods (FFVM and RFVM).

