#### Baseline characteristics

The baseline characteristics of all participants will be presented by study arm in a table (see Table 2), but no formal statistical hypothesis testing will be performed to avoid unnecessary testing.

**Table 2 Tab2:** Baseline characteristics of study participants

	FFVM	RFVM
Patients		
Age, years: mean (SD)	xx.x (xx.x)	xx.x (xx.x)
Age ≥ 65 years: *n*/total *n* (%)	x/x (xx.x)	x/x (xx.x)
Female gender: *n*/total *n* (%)	x/x (xx.x)	x/x (xx.x)
Charlson comorbidity index: median (IQR)	xx.x (xx.x-xx.x)	xx.x (xx.x-xx.x)
History of dementia: *n*/total *n* (%)	x/x (xx.x)	x/x (xx.x)
Hazardous alcohol consumption:^a^ *n*/total *n* (%)	x/x (xx.x)	x/x (xx.x)
ICU admission type		
Medical: *n*/total *n* (%)	x/x (xx.x)	x/x (xx.x)
Emergency surgery: *n*/total *n* (%)	x/x (xx.x)	x/x (xx.x)
Elective surgery: *n*/total *n* (%)	x/x (xx.x)	x/x (xx.x)
PRE-DELIRIC score: mean (SD)	xx.x (xx.x)	xx.x (xx.x)
APACHE-II score:^b^ mean (SD)	xx.x (xx.x)	xx.x (xx.x)
SOFA score:^b^ mean (SD)	xx.x (xx.x)	xx.x (xx.x)
Mechanically ventilated: *n*/total *n* (%)	x/x (xx.x)	x/x (xx.x)
Use of vasopressor: *n*/total *n* (%)	x/x (xx.x)	x/x (xx.x)
Use of corticosteroids: *n*/total *n* (%)	x/x (xx.x)	x/x (xx.x)
Use of parenteral sedative:^b^ *n*/total *n* (%)	x/x (xx.x)	x/x (xx.x)
Use of benzodiazepine:^b^ *n*/total *n* (%)	x/x (xx.x)	x/x (xx.x)
Use of opioid:^b^ *n*/total *n* (%)	x/x (xx.x)	x/x (xx.x)
Indwelling central venous catheter: *n*/total *n* (%)	x/x (xx.x)	x/x (xx.x)
Urinary catheter: *n*/total *n* (%)	x/x (xx.x)	x/x (xx.x)
Family members		
Age, years: mean (SD)	xx.x (xx.x)	xx.x (xx.x)
Female gender: *n*/total *n* (%)	x/x (xx.x)	x/x (xx.x)
Years of education: mean (SD)	xx.x (xx.x)	xx.x (xx.x)
Household income, USD: median (IQR)	xx.x (xx.x-xx.x)	xx.x (xx.x-xx.x)
Unemployed: *n*/total *n* (%)	x/x (xx.x)	x/x (xx.x)
Living with care recipient: *n*/total *n* (%)	x/x (xx.x)	x/x (xx.x)
Surrogate decision maker: *n*/total *n* (%)	x/x (xx.x)	x/x(xx.x)
History of anxiety: *n*/total *n* (%)	x/x (xx.x)	x/x (xx.x)
History of depression: *n*/total *n* (%)	x/x (xx.x)	x/x (xx.x)
ICU professionals		
Age, years: mean (SD)	xx.x (xx.x)	xx.x (xx.x)
Female gender: *n*/total *n* (%)	x/x (xx.x)	x/x (xx.x)
Type of ICU professional		
Physician: *n*/total *n* (%)	x/x (xx.x)	x/x (xx.x)
Nurse: *n*/total *n* (%)	x/x (xx.x)	x/x (xx.x)
Nurse technician: *n*/total *n* (%)	x/x (xx.x)	x/x (xx.x)
Physiotherapist: *n*/total *n* (%)	x/x (xx.x)	x/x (xx.x)

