#### Primary outcome

All the pre-specified study outcomes are described in Table 3. The primary outcome is the cumulative incidence of delirium during ICU stay determined by the CAM-ICU, which was validated for the Brazilian population of critical care patients [21]. The cumulative incidence of delirium is defined as the presence of delirium (at least one positive CAM-ICU score) during the ICU stay. The differences in the incidences of delirium between the FFVM and the RFVM groups will be compared using generalized estimating equations with adjustment for the cluster effect, period effect, and interaction between intervention and period and presented as risk ratio (RR) and 95% CI.

**Table 3 Tab3:** Study outcomes

Outcomes	FFVM	RFVM	Type of effect estimate	Effect estimate (CI)	*p* value^a^
Primary					
Cumulative incidence of delirium:^b^ *n*/total *n* (%)	x/x (xx.x)	x/x (xx.x)	RR	x.xx (x.xx-x.xx)*	x.xx
Secondary					
Patients					
Daily hazard of delirium:^b^ mean (SD)	xx.x (xx.x)	xx.x (xx.x)	HR	x.xx (x.xx-x.xx)**	x.xx
Any ICU-acquired infection:^c^ *n*/total *n* (%)	x/x (xx.x)	x/x (xx.x)	RR	x.xx (x.xx-x.xx)*	x.xx
Proportion of ventilator free-days: mean (SD)	xx.x (xx.x)	xx.x (xx.x)	MD	x.xx (x.xx-x.xx)**	x.xx
ICU length of stay: mean (SD)	xx.x (xx.x)	xx.x (xx.x)	MD	x.xx (x.xx-x.xx)**	x.xx
Hospital mortality: *n*/total *n* (%)	x/x (xx.x)	x/x (xx.x)	RR	x.xx (x.xx-x.xx)**	x.xx
Family members					
HADS anxiety score: mean (SD)	xx.x (xx.x)	xx.x (xx.x)	MD	x.xx (x.xx-x.xx)***	x.xx
HADS depression score: mean (SD)	xx.x (xx.x)	xx.x (xx.x)	MD	x.xx (x.xx-x.xx)***	x.xx
CCFNI satisfaction score: mean (SD)	xx.x (xx.x)	xx.x (xx.x)	MD	x.xx (x.xx-x.xx)***	x.xx
ICU professionals					
Burnout syndrome:^d^ *n*/total *n* (%)	x/x (xx.x)	x/x (xx.x)	PR	x.xx (x.xx-x.xx)*	x.xx
Tertiary					
Patients					
Need for antipsychotic agents: *n*/total *n* (%)	x/x (xx.x)	x/x (xx.x)	RR	x.xx (x.xx-x.xx)*	x.xx
Need for mechanical restraints: *n*/total *n* (%)	x/x (xx.x)	x/x (xx.x)	RR	x.xx (x.xx-x.xx)*	x.xx
Unplanned loss of invasive devices: *n*/total *n* (%)	x/x (xx.x)	x/x (xx.x)	RR	x.xx (x.xx-x.xx)*	x.xx
Proportion of coma-free days: mean (SD)	xx.x (xx.x)	xx. (xx.x)	MD	x.xx (x.xx-x.xx)*	x.xx
ICU-acquired pneumonia:^c^ *n*/total *n* (%)	x/x (xx.x)	x/x (xx.x)	RR	x.xx (x.xx-x.xx)*	x.xx
ICU-acquired UTI:^c^ *n*/total *n* (%)	x/x (xx.x)	x/x (xx.x)	RR	x.xx (x.xx-x.xx)*	x.xx
ICU-acquired BSI:^c^ *n*/total *n* (%)	x/x (xx.x)	x/x (xx.x)	RR	x.xx (x.xx-x.xx)*	x.xx
Family members					

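### The model for unplanned device loss leaves out baseline catheter status, which is already collected, so an enrolment imbalance could shift the risk ratio modestly and prognostic information goes unused

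*SAP article*

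**What the plan says.** The SAP article, Tertiary outcomes, defines the outcome as the "cumulative incidence of any unplanned loss of invasive devices (venous catheter, enteral tube, or urinary catheter) during the ICU stay". The model adjusts for cluster, period and the intervention-by-period interaction, and the result is an RR with a 95% CI. No device variable appears, and no denominator is named for this outcome.

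The denominator has to be inferred from the general rules. Overall principles says that "all participants with a recorded outcome will be included in the analysis", and Definition of analysis sets says: "At the subject level, the ITT population includes all participants, regardless of protocol deviations". Table 3 gives a count over a total for this outcome without saying who makes up the total.

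Table 2 lists "Indwelling central venous catheter" and "Urinary catheter" among the baseline characteristics of patients. It has no row for enteral tubes or for venous catheters other than central ones.

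The caption of Fig. 1 says that each ICU works under its assigned model for a 15-day learning period before it recruits in each phase. Tertiary outcomes are declared exploratory and unadjusted for multiplicity. The main safety outcomes are ICU-acquired infection and burnout (Secondary outcomes).

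**The concern.** Only a patient with one of the listed devices can lose one, so device carriage at inclusion should be a strong predictor of this outcome. Two of the relevant device types are recorded at baseline, and the model uses neither.

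The visiting model is known when patients are enrolled. Table 1 also contains exclusions that involve judgement or circumstance, such as a predicted short stay or having no relative available for flexible visits. Device carriage at inclusion could therefore differ between models beyond chance, and this would move the RR without any effect of visiting.

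The plan already adjusts for baseline status elsewhere. Burnout is adjusted for the baseline Maslach Burnout Inventory score. Sensitivity analyses adjust the family anxiety and depression scores for previous history, and the primary outcome for the PRE-DELIRIC score. Device loss is the outcome to which the two catheter variables bear most directly.

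**Working it through.** The SAP article gives no rate, sample size or power for this outcome, so there is no figure to reproduce. The device shares, loss risks and design effects below are assumptions for illustration.

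**Size.** Abstract and Trial overview: 40 ICUs, 25 patients per ICU and phase, each ICU serving under both models. If recruitment is complete, 40 × 25 = 1000 patients per model.

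**1. Shift from a baseline imbalance with no visiting effect.** Assume a loss risk of 6% in patients with a catheter at inclusion and 1% in the others. With share *p* carrying a catheter, risk = 0.06*p* + 0.01(1 − *p*).

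| Share, flexible vs restrictive | Risks | RR |
|---|---|---|
| 63% vs 60% | 0.0415 / 0.0400 | 1.04 |
| 65% vs 60% | 0.0425 / 0.0400 | 1.06 |
| 70% vs 60% | 0.0450 / 0.0400 | 1.13 |

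**2. How likely such gaps are by chance.** The standard error of the difference in shares is √[(p₁(1−p₁) + p₂(1−p₂))/1000].
- 63% vs 60%: √[(0.2331 + 0.2400)/1000] = 0.0218, so the gap is 0.03/0.0218 = 1.4 standard errors.
- 65% vs 60%: √[(0.2275 + 0.2400)/1000] = 0.0216, so 2.3 standard errors.
- 70% vs 60%: √[(0.2100 + 0.2400)/1000] = 0.0212, so 4.7 standard errors, or 4.7/√3 = 2.7 at an assumed design effect of 3.

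Chance can readily produce the first gap. The last would need a systematic difference in who is enrolled.

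**3. Sensitivity to the assumptions.** If only carriers can have the event, RR(all) = RR(carriers) × p_F/p_R, where p_F and p_R are the shares with a device under the flexible and restrictive models. The 95% chance range of p_F/p_R is exp(±1.96√[2(1−p)/(1000p) × design effect]):
- 90% carriage, design effect 1: 0.97 to 1.03
- 50% carriage, design effect 2: 0.88 to 1.13
- 30% carriage, design effect 3: 0.79 to 1.26

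With equal carriage the factor is 1 and nothing is distorted.

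**4. Against sampling error.** At a 4% risk and 1000 per model, SE(log RR) = √[2 × 0.96/(0.04 × 1000)] = 0.219. The 95% CI factor is exp(1.96 × 0.219) = 1.54 before any design effect. All three shifts in step 1 lie well inside it.

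**5. A masking example.** Take carriage of 50% under the flexible model and 60% under the restrictive one, with loss among carriers of 7% and 6% (RR 0.07/0.06 = 1.17). The all-patient risks are 0.5 × 0.07 + 0.5 × 0.01 = 0.040 and 0.6 × 0.06 + 0.4 × 0.01 = 0.040, so RR = 1.00. As a chance baseline gap, this is 0.10/√[(0.25 + 0.24)/1000] = 4.5 standard errors, or about 2.6 at a design effect of 3.

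**The case against.** The strongest reply is that nothing here is invalid. The all-patient RR follows the plan's own intention-to-treat rule and estimates the total effect of the visiting model on device loss. Every ICU is planned to serve under both models, so stable differences between ICUs in device use largely cancel. Patients are enrolled consecutively, and nothing in the article shows that device use differs between models. Chance imbalance is already part of the sampling error that the CI reflects. Table 2 reports both catheters by arm, so readers would see an imbalance. All of this stands.

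A reader might go further than the documents allow in two ways.

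- **That a difference in device use would be mistaken for a safety effect, or would hide one, as in step 5.** If flexible visiting changes device use during the stay, that change is part of the policy's effect and not confounding, and baseline covariates could not remove it. If the 10-point gap existed at baseline, it is too large to be a plausible chance finding.
- **That restricting to patients with a catheter at inclusion gives the at-risk analysis.** It does not. The outcome covers enteral tubes and venous catheters of any kind, while Table 2 has only central venous and urinary catheters and misses devices placed later. Restricting to devices carried during the stay would condition on something that happens after allocation.

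The objection does not answer two smaller points. Systematic imbalance through enrolment under a known visiting model is not covered by the CI, and showing it in Table 2 does not adjust for it. The denominator can be inferred from the general rules but is not stated for this outcome.

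**Conclusion.** The point holds as a minor one. The model omits two baseline variables that are collected and that bear directly on the outcome. A baseline imbalance could shift the RR by about 1.04 to 1.13 on the assumed 6% and 1% loss risks and carriage of 63% to 70% against 60%. The upper end would need enrolment imbalance rather than chance. If nearly all patients carry a device and the mix is balanced, the shift is negligible and the gain is a modest one in precision.

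The all-patient RR is not biased by design, and the article does not support a claim that the comparison is unsound. The outcome is exploratory and not a main safety outcome, so no conclusion about the primary outcome or the main safety outcomes depends on it.

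**What to change.** In Tertiary outcomes, under unplanned loss of invasive devices:

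1. State that the denominator is all participants, and keep the all-patient RR.
2. Add baseline central venous catheter and baseline urinary catheter as covariates in the model, or report this adjusted RR beside the unadjusted one.
3. Optionally, report the RR among patients with either catheter at inclusion as supportive only. Note that this is not the full at-risk set, because enteral tubes, other venous lines and devices placed later are not captured.
4. Note that neither analysis separates out an effect of visiting on device use during the stay.

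The cost is a sentence or two of SAP wording, slightly more analysis work, and two extra parameters for an outcome that may be infrequent. No new data are needed. The optional analysis would rest on fewer patients.

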### Differences between the study protocol and statistical analysis plan

There are no differences between the study protocol and this SAP in relation to the proposed outcomes or statistical procedures.

## Discussion and trial status

In this SAP, we present the statistical procedures that will allow the comparison of effectiveness and safety outcomes between the FFVM and RFVM in the ICU Visits Study. The present publication aims to avoid risks of outcome reporting bias and data-driven results and provide guidance for statistical analysis for future studies in this field. As of March 2018, 40 ICUs were randomized. Currently, 1591 patients, 1192 family members, and 829 ICU professionals were included in the study. We expect that the recruitment of subjects will be completed in June 2018.

## Abbreviations

APACHE-II: Acute Physiology and Chronic Health Evaluation-II
BSI: Bloodstream infection
CAM-ICU: Confusion Assessment Method for the Intensive Care Unit
CCFNI: Critical Care Family Needs Inventory
CDC: Centers for Disease Control and Prevention
CI: Confidence interval
CONSORT: Consolidated Standards of Reporting Trials
FFVM: Flexible family visitation model
HADS: Hospital Anxiety and Depression Scale
HR: Hazard ratio
ICU: Intensive care unit
IQR: Interquartile range
MBI: Maslach Burnout Inventory
MD: Mean difference
PR: Prevalence ratio
PRE-DELIRIC: PREdiction of DELIRium in ICU patients
RASS: Richmond Agitation-Sedation Scale
RFVM: Restrictive family visitation model
RR: Risk ratio
SAP: Statistical analysis plan
SD: Standard deviation
SOFA: Sequential Organ Failure Assessment
USD: United States dollars
UTI: Urinary tract infection
